## 4. STATISTICAL ANALYSES

### 4.1. STATISTICAL SOFTWARE

The latest version of STATA, supported by the University of Bristol, will be used for all statistical analyses specified in this plan.

### 4.2. RECRUITMENT AND RETENTION

A CONSORT flowchart will give details of participant recruitment and flow through the study (**Figure 1**, see Section 5). Summary statistics for baseline measures, presented by allocated group, will characterise the study sample (**Table 1**, see Section 5). Supplementary material will give details of recruiting site (**Supplementary Table 1**), and the initial consultation (**Supplementary Table 2**). Details of formal full study withdrawals are presented in **Supplementary Table 8** (see Section 5).

### 4.3. ANALYSIS OF THE PRIMARY OUTCOME

Analysis of the primary outcome will be conducted on complete data, using the intention to treat principle and appropriate regression model. Model assumptions will be checked and alternative approaches considered if there is concern that estimates may be biased.

The primary outcome, prescription of an antibiotic at appointment 2 on day 1, will be compared between the two allocated groups, POCT versus no POCT, using a logistic regression model with covariates distinguishing the two allocated groups, the two age groups (< 16 years old versus ≥ 16 years old), and chronic lung disease status (present versus absent). The odds ratio, 95% confidence interval and p-value will be presented (**Table 2**, see Section 5).

### 4.4. SUBGROUP ANALYSES FOR PRIMARY OUTCOME

Three pre-specified subgroup analyses will be conducted for the primary outcome (**Table 2**, see section 5):

Age <16 years versus 16+ years. We hypothesize that, due to less information about symptoms being provided by children, the information from the POCTRM will reduce antibiotic prescriptions to a greater extent in children.

Presence or absence of chronic lung disease. We hypothesize that general practitioners will tend to “play it safe” and prescribe an antibiotic to those with chronic lung disease, and there will be less of an impact of the POCTRM on antibiotic prescribing in that group.

Disagreement (or not) between the general practitioner and the patient in whether an antibiotic is needed. We hypothesize there will be a greater impact of the POCTRM in reducing antibiotic prescribing when the patient believes an antibiotic is needed (agree or strongly agree with this statement) but the general practitioner strongly disagrees or disagrees that an antibiotic is needed,

or is uncertain. In this situation, evidence from the POCTRM that the RTI may have a viral cause may reduce the likelihood of the general practitioner being persuaded to prescribe an antibiotic.

If there is evidence of superiority for the POCTRM group compared to the control group on the key secondary outcome of symptom severity over days 2 to 4, the above subgroup analyses will also be conducted for that measure (and presented in a separate supplementary table).

#### 4.5. ANALYSIS OF THE KEY SECONDARY OUTCOME

The key secondary outcome, participant reported mean symptom severity on days 2 to 4, will be compared between the two allocated groups, POCT versus no POCT, using a mixed linear regression model with covariates distinguishing the allocated groups, the two age groups (< 16 years old versus ≥ 16 years old) and chronic lung disease status (present versus absent), and a random effect at the participant level to accommodate the correlation between the three repeated responses per participant. Keeping the symptom scores separate as three repeated measures, rather than taking an average symptom score over the three days, provides greater transparency in the accommodation of patients who have reported symptoms on only one or two of the three days.

For comparability with previous studies in this area, the estimator will be the difference between the allocated groups in the average symptom score over days 2, 3 and 4. The coefficient of the covariate distinguishing the allocated groups, described in the previous paragraph, will provide this estimator. The distribution of residuals will be checked, and if markedly non-normal, the use of bias-corrected and accelerated bootstrap confidence intervals will be considered.

If a one-sided 95% confidence interval excludes increases of 20% or greater in the mean symptom score reported by the group allocated to POCT, then the POCT group will be considered non-inferior. A two-sided 95% confidence interval and p-value will also be presented to allow comparison with other studies, and inference about superiority of the POCT group in the event that non-inferiority is demonstrated (**Table 3**, see Section 5).

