### 6.4 Appointment One (Day 1)

#### *Figure 1, Step 2*

Appointment One will be held either face-to-face or remotely (via a video/phone call). The Study Clinician will assess the patient as per usual clinical care up to (but not including) making the final antibiotic treatment decision which must be deferred until Step 5. The Study Clinician will complete their Study Clinician views (see Appendix 1, Study Clinician Views questions 1 to 5) and then determine eligibility and willingness to take part. The Study Champion or the Study Clinician will take consent (see below) and collect demographic and clinical data. They will also provide the participant or parent/carer with the Trial Diary, either online or in paper format according to participant preference and ask the patient to complete Part A on baseline symptoms and Part B on the EQ-5D. If the patient (or parent/carer if the patient is <16 years) declines to take part in the trial, the reason for this (if provided) will be collected along with brief non-identifiable data including age. Patients who decline will be returned to standard care.

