### 2.10.2. CLINICAL SECONDARY OUTCOMES

**Participant-completed symptom diaries** at baseline (day 1, pre-randomisation) and for 28 days afterwards (first post-randomisation completion on day 1 after appointment 2). Ten symptoms were completed by all participants: blocked nose, fever, shortness of breath, phlegm, wheeze, eating or drinking less than normal, disturbed sleep, ear pain and change in voice. Those age 16+ years completed four further symptoms: sore throat, muscle facial or head aching or pain, sweats or chills, and unable to do usual activities e.g. work school childcare etc. Those age under 16 years completed one additional item: child not themselves or more clingy than usual. Each item was responded to using the following seven-point scale:

- 0 = Normal/not affected
- 1 = Very little problem
- 2 = Slight problem
- 3 = Moderately bad
- 4 = Bad
- 5 = Very bad
- 6 = As bad as it could be

Participants are instructed to stop completing the diary once they have two consecutive days for which all symptoms are rated at zero, or once 28 days have been completed.

For any diary days that have been partially completed, with at least one symptom completed, symptoms left blank will assumed to be scored as zero (i.e. the symptom is completely resolved). Any days with no symptoms rated will be considered as missing data.

In addition participants were asked to record in the daily diaries if they were taking an antibiotic, which one, and how many doses were taken each day.

The following measures were derived from participant-completed symptom diaries:

| Diary measures                                                                         | Type       | Outcome detail                                                                                                                                                                                                                                                                                                                               |
|----------------------------------------------------------------------------------------|------------|----------------------------------------------------------------------------------------------------------------------------------------------------------------------------------------------------------------------------------------------------------------------------------------------------------------------------------------------|

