#### 4.6. SENSITIVITY ANALYSES

The following sensitivity analyses will be performed:

1. For the primary outcome only, an analysis based on the per protocol analysis set.
2. For the primary outcome and key secondary outcome, the analysis will be repeated with additional covariates to (i) distinguish the recruiting practices, and (ii) to include any baseline variables observed to be imbalanced (>10 percentage points difference for binary measures, >0.5 standard deviations difference between means for continuous measures).
3. For the key secondary outcome only, to investigate the potential effect of data being missing not at random, the analysis will be repeated (i) excluding participants at two practices with <60% completion rates of diary data for days 2 to 4, and (ii) imputing missing ratings with the individual's baseline assessment for the POCTRM group, and a score of zero for the comparison group. The resulting intervention effect estimate only will be presented in the text, as an indication of the extent to which missing data may be affecting the ITT estimate.

See **Table 2** and **Table 3**, Section 5.

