| Other symptom measures                           | Mean (SD), n                 | Mean (SD), n            | Difference in meansc
(95% confidence interval) | P value |
| Duration of moderately bad, or worse, symptoms          | X.X (X.X), X                        | X.X (X.X), X                   | XX.XX (XX.XX, XX.XX)                                                 | 0.XXX          |
| Time to return to usual activities (adults 16+ years)   | X.X (X.X), X                        | X.X (X.X), X                   | XX.XX (XX.XX, XX.XX)                                                 | 0.XXX          |
| Time to return to usual activities (children <16 years) | X.X (X.X), X                        | X.X (X.X), X                   | XX.XX (XX.XX, XX.XX)                                                 | 0.XXX          |
| Overall symptom duration                                | X.X (X.X), X                        | X.X (X.X), X                   | XX.XX (XX.XX, XX.XX)                                                 | 0.XXX          |
|                                                         | n/N (%)                      | n/N (%)                 | Odds ratioa
(95% confidence interval)          | P value |
| Participant experiences worsening symptoms              | XX/XXX (XX%)                        | XX/XXX (XX%)                   | XX.XX (XX.XX, XX.XX)                                                 | 0.XXX          |

a. All estimates adjusted for participant age and chronic lung disease status

b. One-sided 95% confidence interval, for establishing non-inferiority, presented in the text

c. Bias-corrected and accelerated bootstrap confidence intervals, non-parametric p-value

**Table 4.** Further healthcare contacts post-randomisation

|                                                                                                  |    | Intervention
N (%) | Control
N (%) | Odds ratio*
(95% confidence interval) | P value* |
|--------------------------------------------------------------------------------------------------|----|-----------------------|------------------|------------------------------------------|----------|
| Number (%) of patients hospitalised for RTI one or more times between appointment two and day 28 |    | XX (XX%)              | XX (XX%)         | XX.XX (XX.XX, XX.XX)                     | 0.XXX    |

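### The key secondary non-inferiority model omits the pre-randomisation symptom score, so it gives up precision that data already collected would supply

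*Combined protocol and SAP*

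**What the plan says.** SAP 4.5 fits the day 2, 3 and 4 scores "using a mixed linear regression model with covariates distinguishing the allocated groups, the two age groups" and chronic lung disease status, plus "a random effect at the participant level to accommodate the correlation between the three repeated responses per participant". Footnote a to the Table 3 shell confirms the adjustment set: "All estimates adjusted for participant age and chronic lung disease status". On the target, SAP 4.5 states that "the estimator will be the difference between the allocated groups in the average symptom score over days 2, 3 and 4".

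A baseline value of the same measure exists. SAP 2.10.2 has the diary completed "at baseline (day 1, pre-randomisation) and for 28 days afterwards", and protocol 6.4 has the participant "complete Part A on baseline symptoms and Part B on the EQ-5D" at Appointment One. The Table 1 shell covers demographics, medical history, clinical measures, signs, diagnosis and the clinician's overall assessment, but no symptom score.

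SAP 4.6 touches baseline data in two places. Sensitivity analysis 2(ii) adds baseline variables found to be imbalanced, defined as ">0.5 standard deviations difference between means for continuous measures". Sensitivity analysis 3(ii) fills missing ratings with the participant's own baseline in the POCT arm and with zero in the control arm; only the resulting estimate is reported.

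**The concern.** A pre-randomisation measurement on the same scale is usually among the best predictors of a symptom score a few days later. Leaving it out widens the confidence interval on which the non-inferiority claim rests, and that claim supports the statement that less prescribing does not worsen symptoms. The plan is also uneven: Supplementary Tables 3c and 3d adjust participant views for baseline views, while the key secondary outcome gets no such adjustment.

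The second issue is missing diaries. The sample size allows for 20% loss and participants know their allocation. A likelihood-based model handles missing data only through the variables it contains. If loss depended on initial severity, and did so differently in the two arms, a model without baseline would be biased.

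**Working it through.** **1. Can baseline enter as a covariate?** It is not in the main model. Under 2(ii), with 514 randomised 1:1 (257 per group), the standard error of a baseline difference in SD units is sqrt(2/257) = 0.0882. A 0.5 SD difference is then 0.5/0.0882 = 5.67 standard errors, a chance of about 1 in 10^8. Even if triggered, it would add only a sensitivity analysis.

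**2. The plan's own figure.** Inputs from SAP 2.7: CV 0.7, margin 20%, one-sided 5%, power 90%, true difference zero. On the log scale:

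- SD = sqrt(ln(1 + 0.7²)) = 0.6315; margin = ln(1.2) = 0.1823
- n = 2 × (1.645 + 1.282)² × 0.6315² / 0.1823², which rounds up to 206 per group
- power at 206 = Phi(0.1823/(0.6315 × sqrt(2/206)) - 1.645) = Phi(1.285) = 90.1%

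The stated 206 and 90% reproduce with no baseline adjustment.

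**3. Precision with baseline.** Let r be the correlation between the baseline score and the days 2 to 4 mean. Residual variance is multiplied by (1 - r²). The documents do not give r, so a range is shown. The last column is 1.645 × 1.5 × sqrt(2/206) × sqrt(1 - r²), in score points, using the documents' SD of 1.5. The margin is 20% of 2.3 = 0.46.

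| r | 1 - r² | Power at 206 per group | n per group for the same power, 206(1 - r²) | Estimate to one-sided bound |
|---|---|---|---|---|
| 0 | 1.00 | 90.1% | 206 | 0.243 |
| 0.3 | 0.91 | 92.3% | 188 | 0.232 |
| 0.5 | 0.75 | 95.9% | 155 | 0.211 |
| 0.6 | 0.64 | 97.8% | 132 | 0.195 |

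On the raw scale (SD 1.5, margin 0.46) power starts at 92.9% and rises to 94.7%, 97.4% and 98.8%, so the pattern does not depend on the scale.

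**4. Diary loss.** Simulations set the true difference to zero, with about 20% loss and normal scores. Loss followed a logistic model with slope b per baseline SD. These settings are illustrative. Bias is POCT minus control, so negative values favour non-inferiority.

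| Assumed loss | Model as planned | With baseline |
|---|---|---|
| Completely at random, or same relation to baseline in both arms | about 0 | about 0 |
| Sicker lost in both arms, more strongly in POCT (b = 0.5 and 0.25, r = 0.5) | -0.04 | not run |
| Sicker lost, POCT only (b = 0.8, r = 0.3 to 0.5) | -0.07 to -0.11 | about 0 |
| Opposite relations by arm (b = 0.8, r = 0.3 to 0.5) | -0.13 to -0.23 | about 0 |
| Opposite relations, signs reversed (b = 0.5, r = 0.5) | +0.14 | not run |
| Depends on the unseen outcome, POCT only | -0.18 to -0.19 | -0.13 to -0.17 |

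A rough hand check for one arm is bias ≈ -r × SD × b × proportion lost. For r = 0.3, b = 0.8: -0.3 × 1.5 × 0.8 × 0.2 = -0.07. For r = 0.5, b = 0.8: -0.12, doubling to -0.24 with opposite relations. These agree with the simulated -0.07, -0.11 and -0.23. Against the margin, 0.07/0.46 = 15% and 0.23/0.46 = 50%.

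**5. Day.** Adding day left the standard error unchanged (0.1375 with and without it). With scores falling 0.3 per day, and day 3 and day 4 loss of 25% and 35% in POCT against 5% and 10% in control, the planned model was biased by +0.06, against non-inferiority. A day main effect removed this.

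**The case against.** The planned model is pre-specified, adjusts for the stratification factors, and is unbiased under randomisation unless loss differs by arm. The sample size was set without any gain from baseline, so nothing falls short. All of that stands. A reader might infer that the trial is underpowered or the calculation wrong; step 2 shows neither is so.

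The plan also probes missing data. Sensitivity analysis 3(ii) is deliberately hostile to POCT: with 20% missing per arm and an assumed baseline mean of 2.3, setting control gaps to zero moves the difference by about 0.2 × 2.3 = +0.46, the whole margin. That is a real safeguard, so it would be wrong to say baseline is unused. But 3(ii) uses it only to impute POCT ratings, reports only an estimate, and adds no precision to the main analysis.

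A reader might also infer that the non-inferiority estimate is biased towards POCT. The documents do not support that. They give no diary loss by arm or by severity. The two practices that SAP 4.6 names for completion below 60% show loss varying by practice, which is a different matter. The bias vanishes when the relation to baseline is the same in both arms, and changes sign when the arms are swapped. The near-zero bias after adjustment is also built into scenarios where loss depends only on baseline.

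Finally, a reader might infer that omitting day costs precision. It does not. With all three days reported, the group coefficient already is the three-day average difference.

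**Conclusion.** The point holds as avoidable loss of efficiency in the key secondary analysis, not as an error in it. The gain is from 90.1% power to about 92%, 96% or 98% for assumed correlations of 0.3, 0.5 and 0.6; its size cannot be fixed from the documents. Protection against loss related to baseline differently by arm is a secondary benefit, worth -0.07 to -0.23 points in the one-arm and opposite-relation scenarios and nothing when the arms behave alike. Adjustment does not deal with loss that depends on unseen outcomes, so it does not replace sensitivity analysis 3. The day term is a minor, optional matter of matching the model to its stated target; the one distortion simulated was small and conservative. The change is worth making because it uses a value already collected.

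**What to change.** - In SAP 4.5, add the pre-randomisation mean symptom score, built from the same items and denominator as the daily scores, as a covariate. Pre-specify a simple rule for missing baseline scores, such as mean imputation.
- Add the baseline score to Table 1 and amend footnote a of Table 3.
- Keep the current model as a sensitivity analysis, and keep sensitivity analysis 3.
- Optionally, add day (2, 3, 4) as a categorical main effect. SAP 4.5 separates the days for the "accommodation of patients who have reported symptoms on only one or two of the three days", and without a day effect such participants stand in for the three-day average. No group-by-day interaction is needed for the single estimate planned.

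The cost is SAP wording, with no new data. The one downside is the rule for missing baseline diaries, whose number the documents do not state. The change should be settled before the first database lock, since protocol 6.11 has the Trial Management Group review unblinded key secondary data after it.

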#### 4.6. SENSITIVITY ANALYSES

The following sensitivity analyses will be performed:

1. For the primary outcome only, an analysis based on the per protocol analysis set.
2. For the primary outcome and key secondary outcome, the analysis will be repeated with additional covariates to (i) distinguish the recruiting practices, and (ii) to include any baseline variables observed to be imbalanced (>10 percentage points difference for binary measures, >0.5 standard deviations difference between means for continuous measures).
3. For the key secondary outcome only, to investigate the potential effect of data being missing not at random, the analysis will be repeated (i) excluding participants at two practices with <60% completion rates of diary data for days 2 to 4, and (ii) imputing missing ratings with the individual's baseline assessment for the POCTRM group, and a score of zero for the comparison group. The resulting intervention effect estimate only will be presented in the text, as an indication of the extent to which missing data may be affecting the ITT estimate.

See **Table 2** and **Table 3**, Section 5.

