## 2.7. SAMPLE SIZE CALCULATION

Assuming an antibiotic prescribing rate of 60% in the control group, 244 participants per group will allow a true reduction to 45% in the POCT group to be detected with 90% power at 5% significance. A total randomisation target of 514 will allow for 5% attrition. This number will provide at least 90% power to detect the same absolute difference if the antibiotic prescribing rate is found to be higher or lower than 60% in the control group.

If the POCT results in fewer antibiotic prescriptions, we wish to demonstrate non-inferiority of the POCT in terms of not increasing mean symptom severity at days 2 to 4 to a clinically significant extent. Assuming 80% completion of Trial Diaries (as previously achieved in adults and children) we will have data for symptom severity at 2 to 4 days in 206 participants per group. Data on 7,000 adults and children managed without POCT indicates a mean symptom severity at days 2 to 4 of 2.3 (standard deviation 1.5). We know this measure's distribution is positively skewed and have used a calculation that accommodates this (assuming equal skew in both groups, quantified as a coefficient of variation of 0.7). Assuming, in truth, no difference between groups, 206 participants in each group will give 90% power for a one-sided 95% confidence interval to exclude increases in the average symptom score of 20% or more.

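### The missing-not-at-random check for days 2 to 4 symptom severity is one extreme scenario without a confidence interval, and days left blank after the instructed diary stop count as missing

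*Combined protocol and SAP*

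**What the plan says.** SAP 4.5 judges the key secondary outcome, mean symptom severity on days 2 to 4, for non-inferiority: "If a one-sided 95% confidence interval excludes increases of 20% or greater in the mean symptom score reported by the group allocated to POCT", the POCT group is taken to be non-inferior.

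SAP 4.6 item 3 gives two checks meant to examine data missing not at random (MNAR):

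- Item 3(i) repeats the analysis "excluding participants at two practices with <60% completion rates of diary data for days 2 to 4".
- Item 3(ii) replaces missing ratings with the participant's own baseline in the POCT "group, and a score of zero for the comparison group". Only the resulting estimate is to be given, in the text. SAP Table 3 has a row with a confidence interval and p-value for 3(i), but none for 3(ii).

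On diary scoring, SAP 2.10.2 says: "Participants are instructed to stop completing the diary once they have two consecutive days for which all symptoms are rated at zero"; otherwise the diary runs to day 28. It then says: "Any days with no symptoms rated will be considered as missing data". Blank items are set to zero only on days with at least one item completed. No rule covers days after the instructed stop.

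SAP 2.7 plans on 80% diary completion. The protocol's Trial Summary lets recruitment continue until at least 80% of participants have complete diary data for days 2 to 4.

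**The concern.** If the test reduces prescribing, non-inferiority on symptoms is what lets that reduction be called safe. Diaries are filled in by unblinded participants and about one in five may be incomplete, so informative dropout is a main threat to that conclusion. Protocol 10.2 promises sensitivity analyses that gauge robustness to different missing-data assumptions.

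Item 3(ii) offers one assumption, close to the worst for POCT and the best for control. If the filling-in by itself moves the estimate by about the size of the margin, an adverse result cannot be told apart from the arithmetic of the imputation. Item 3(i) changes who is analysed but assumes nothing different about unobserved scores. The scoring rule adds a smaller problem: someone who recovers and stops as told is treated as a non-responder, and 3(ii) then fills those days differently in the two groups.

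**Working it through.** **Inputs.** From SAP 2.7: mean 2.3, standard deviation 1.5, coefficient of variation 0.7, 80% completion, 514 randomised 1:1 (257 per group). From SAP 4.5: margin 20%, which is 0.20 × 2.3 = 0.46 points. Not in the documents: the mean baseline score B of those with missing ratings, so it is varied. Its standard deviation is assumed to be 1.5, and missingness equal in the two groups.

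**The plan's own figure.** On the log scale the standard deviation is √ln(1 + 0.7²) = 0.6315 and the margin is ln 1.2 = 0.1823. With one-sided alpha 0.05, 90% power and no true difference, n = 2 × [(1.645 + 1.282) × 0.6315 / 0.1823]² ≈ 206 per group. Also 0.80 × 257 = 205.6. The stated 206 is reproduced.

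**What item 3(ii) adds.** Let m be the fraction of person-days missing, with observed means of 2.3 in both groups.

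- POCT mean = (1 − m) × 2.3 + m × B
- Control mean = (1 − m) × 2.3
- Difference = m × B

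For the upper bound, take whole diaries as missing. The variance is 1.5² + m(1 − m)(2.3 − B)² for POCT and (1 − m) × 1.5² + m(1 − m) × 2.3² for control. The bound is the difference + 1.645 × √(sum of variances / 257). At m = 20% the control mean is 0.80 × 2.3 = 1.84:

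| B | Added difference | % of 2.3 | % of 1.84 | Expected upper bound | Chance bound passes 0.46 |
|---|---|---|---|---|---|
| 1.0 | 0.20 | 8.7% | 10.9% | 0.43 | 43% |
| 1.5 | 0.30 | 13.0% | 16.3% | 0.53 | 69% |
| 2.0 | 0.40 | 17.4% | 21.7% | 0.63 | 89% |
| 2.3 | 0.46 | 20.0% | 25.0% | 0.69 | 95% |
| 3.0 | 0.60 | 26.1% | 32.6% | 0.83 | 99.6% |

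Simulation with gamma-distributed scores (4,000 trials per row, margin 20% of the observed control mean) gave 45%, 67%, 86%, 93% and 99% for the last column. The SAP does not compute such a bound for 3(ii); the last two columns show what one would look like.

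**Break-even values.** At m = 20% the expected bound passes 0.46 once B exceeds about 1.14. At B = 2.3 it does so once m exceeds about 10%. At m = 20% and B = 2.3, a true POCT benefit of about 0.28 points would be needed for the expected bound just to meet the margin.

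**Partly missing diaries.** Suppose, as an assumption, that half of the incomplete 20% miss all three days and half miss one. Then m = 10% + 10%/3 = 13.3%. At B = 2.3 the addition is 0.133 × 2.3 = 0.31 points. That is 13.3% of 2.3, or 0.133/0.867 = 15.4% of the imputed control mean.

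**Days after the instructed stop.** All-zero days 2 and 3 leave day 4 blank; all-zero days 1 and 2 leave days 3 and 4 blank. Under 3(ii) a POCT participant's blank days take the baseline score and a control's take zero. If an assumed 5% of the POCT group stop this way, at B = 2.3 the added difference is 0.05 × 1/3 × 2.3 = 0.04 (day 4 only) to 0.05 × 2/3 × 2.3 = 0.08 (days 3 and 4). As shares of 2.3 these are 1.7% and 3.3%.

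**The case against.** A reader might infer that the check fails non-inferiority by construction. The documents do not support that, for three reasons.

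- The one-sided rule stands in SAP 4.5 for the main analysis. SAP 4.6 does not apply it to 3(ii), whose estimate is offered only as a guide to how far missing data may matter. A deliberately adverse scenario is legitimate for that purpose.
- The size depends on a baseline mean that the documents do not state, on there being no true POCT benefit, and on which control mean the 20% refers to. At B = 2.3 and m = 20% the addition is exactly at the margin against 2.3, and past it only against 1.84.
- The recruitment target concerns participants with complete days 2 to 4 data. Some of the other 20% will have one or two observed days, which the SAP 4.5 model keeps, so m can be well below 20%.

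All three points stand. They remove the claim of a predetermined failure. They leave the complaint that one extreme scenario, with no interval, cannot show how robust the result is to moderate departures.

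Item 3(i) is also not empty: it asks whether the estimate moves when the practices with the poorest completion are left out. That is a stability check, though not an MNAR analysis.

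A reader might also infer that the stopping rule biases the main comparison. It applies alike to both groups, and those affected still supply at least one observed zero within days 2 to 4. No bias in the between-group difference is shown there; the differential handling arises only inside 3(ii).

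**Conclusion.** The point holds as a weakness of the sensitivity plan, not as a predetermined non-inferiority failure. Item 3(ii) adds m × B points whatever the observed scores show. At 20% missing person-days that is 0.20 to 0.60 points for B from 1.0 to 3.0, against a margin of 0.46. A baseline mean at or above 2.3 is plausible for people presenting with an illness for which antibiotics are being considered, but it is an assumption. With lower baselines or partly completed diaries the shift is smaller. An adverse 3(ii) estimate would therefore be largely uninformative, and without an interval even a favourable one could not be read against the SAP 4.5 rule. Item 3(i) does not fill the gap.

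The scoring rule in SAP 2.10.2 is a real but small inconsistency. It affects only participants who are symptom-free by day 3, a share that is assumed here.

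**What to change.** 1. In SAP 2.10.2, score days after two consecutive all-zero days as zero, not missing.
2. In SAP 4.6, add to or replace 3(ii) with multiple imputation that includes arm, baseline symptom score, age group, chronic lung disease and the observed days. Add a delta to imputed POCT-arm scores over a range stated in advance. Report the delta at which the one-sided 95% bound crosses the 20% margin, and say which control mean the 20% is taken of.
3. If 3(ii) is kept, label it an extreme bound. Describe 3(i) as a stability check.

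The cost is SAP wording and one further imputation analysis; no new data are needed. The delta range has to be justified.
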